## Abstract

**Background:**

Non cephalic presentation in childbirth involves various risks to both the mother and the foetus. The incidence in Spain is 3.8% of all full-term pregnancies. The most common technique used to end the gestation in cases of non cephalic presentation is that of caesarian section, and although it provokes a lower rate of morbi-mortality than does vaginal delivery in such situations, there remains the possibility of traumatic injury to the foetal head and neck, while maternal morbidity is also increased. The application of heat (moxibustion) to an acupuncture point, in order to correct non cephalic presentation, has been practised in China since ancient times, but as yet there is insufficient evidence of its real effectiveness.

**Methods/Design:**

The experimental design consists of a multi-centre randomised controlled trial with three parallel arms, used to compare real moxibustion, sham moxibustion and the natural course of events, among pregnant women with a non cephalic presentation and a gestational duration of 33–35 weeks (estimated by echography). The participants in the trial will be blinded to both interventions. The results obtained will be analyzed by professionals, blinded with respect to the allocation to the different types of intervention. In addition, we intend to carry out a economic analysis.

**Discussion:**

This trial will contribute to the development of evidence concerning moxibustion in the correction of non cephalic presentations. The primary outcome variable is the proportion of cephalic presentations at term. As secondary outcomes, we will evaluate the proportion of cephalic presentations at week 38 of gestation, determined by echography, together with the safety of the technique, the specificity of moxibustion and the control of the blinding process.

This study has been funded by the Health Ministry of the Andalusian Regional Government.

**Trial registration:**

Current Controlled Trials ISRCTN10634508.

## Background

Non cephalic presentation (NCP) in childbirth involves various risks to both the mother and the foetus. NCP includes breech, oblique and transverse presentations. The incidence of breech presentation (BP) is 20% at 28 weeks' gestation, although spontaneous version tends to occur more frequently [1], such that in only 3–4% of women with a full-term pregnancy is the foetus BP [2]; in Spain, NCP represents 3.8% of all births [3].

Until week 28–32, and under normal conditions, the foetus has a high degree of mobility, and remains in an unstable situation. From the latter date, the foetus adapts itself to the shape of the uterus, adopting a head-down posture, and normally remains so until birth. There are various reasons that may prevent the foetus from moving into the cephalic position, the most common of which, according to a specialized study [4] are: a) pre-term birth; this factor is more influential with lower gestational ages (35% before week 28, 16.8% from week 28–31, 8.9% from week 32–36 and 3.7% from week 36–41); b) foetal malformations (those most commonly related to NCP are anencephaly, hydrocephaly, spina bifida, polycystic kidneys and Potter's Syndrome, as well as trisomies 13, 18 and 21; c) multiple pregnancy, in which the incidence of NCP is 7 times greater than in the case of a singleton pregnancy. High levels of perinatal mortality and morbidity are known to be associated with NCP, due mainly to prematurity, congenital malformations, hypoxia or birth trauma [5,6], and so a breech delivery is a birth that is categorized between dystocia and eutocia.

The most common technique used to end gestation in cases of NCP is that of caesarian section. From the results of the study by Hannah et al. [7], in October 2000, from the results produced by the Term Breech Trial Collaborative Group, and from the Cochrane Collaboration review [8], we now know that foetuses which are extracted by elective caesarian section have a lower level of perinatal morbi-mortality than those delivered vaginally. However, this technique does not prevent traumatic lesions to the foetal head and neck and, moreover, it is associated with an increase in maternal morbidity [8-11]. In addition to the increase in morbidity immediately following a caesarean section, there may occur other types of complications, such as intraabdominal adhesions, with the possibility of later infertility and risks in future pregnancies caused by the uterine scar [11].

Due to the risks arising both in breech presentation and from a caesarean section, various manoeuvres have been suggested over the years to promote spontaneous cephalic version of the foetus during the final two months of the pregnancy. Of these actions, the most commonly adopted is that of external cephalic version (ECV), which can be performed either between week 32–34 of gestation, or after week 37. A Cochrane Review concluded that, in comparison with the non-performance of ECV, the latter technique, when begun pre-term, reduces NCP births, while, in comparison with full-term ECV, beginning it between week 34–35 may be of some benefit as concerns the reduction of the rates of NCP and of caesarean section, although further trials were recommended [8]. Other types of manoeuvres and techniques have been tested, with varying degrees of success, in order to increase foetal mobility in a non-traumatic way.

Acupuncture and moxibustion are therapeutic techniques found in traditional Chinese medicine. They have been employed since ancient times, and specific recommendations in Chinese texts include the application of heat (moxibustion) by the combustion of *Artemisia vulgaris *(moxa) over an acupuncture point in order to correct NCP [12,13]. This latter point, known as *Zhiyin *(BL67) is located in the outer corner of the little toenail. In addition to moxibustion, acupuncture may also be used, either alone or in association with moxibustion, on this or other points, although it has been found that the highest level of effectiveness is associated with the application of moxibustion alone [14]. A Cochrane review [15] concluded that there is insufficient evidence from the studies included in its analysis, and observed that there have been few well-designed studies (only 3 are included in the review) and that most of them used a small sample. Some studies with a larger sample, such as that by Kanakura et al. [16], were not randomized. A larger, systematic review that we have carried out this year (manuscript submitted for publication), with the inclusion of new studies performed to date, and with the incorporation of those published in Chinese in the last 10 years, shows that studies contain to be of low methodological quality. We estimate a correction rate of 70% (versus 50% in control groups) among pregnant women treated with moxibustion. Among the studies carried out so far, no reports have been made of side effects, although the smoke generated while the moxa is burned may irritate the respiratory tracts. Nevertheless, there is no evidence to support this hypothesis [15]. Neri et al. [14,17] have made a cardiotocographic study of the effects of moxibustion on foetal heartbeat, and concluded that no harm is caused by this process.

The present study is funded by the Health Ministry of the Andalusian Regional Government (Project No. 0053/2007).

## Methods

### Research aims and questions

The aim of this study is to assess the effects of sensorial stimulation with moxibustion in the outer corner of the little toenail (BL67) in order to produce version in non-cephalic presentations.

### Research questions are

How effective is moxibustion at point BL67 in terms of the rate of full-term cephalic presentations?

How effective is moxibustion at point BL67 in terms of the rate of caesarean sections?

What is the effect of moxibustion at a non-specific point such as SP1 in pregnancies with NCP?

To what extent are the pregnant women to whom the study techniques are applied confident of the outcome?

How safe is the technique in terms of increased rates of changed foetal cardiac rhythm, the risk of premature birth, and changes in APGAR scores at 1 minute and at 5 minutes?

What is the cost-effectiveness of treatment with moxibustion for cases of NCP?

### Duration of Study

April 2008 to December 2010

### Subjects

Pregnant women recruited by their obstetrician during the third scheduled echography (at week 32 of gestation), after confirmation of NCP. These pregnant women will be referred to midwives at the participating Primary Healthcare Clinics belonging to the Andalusian Public Health System in the provinces of Sevilla, Huelva, Cádiz and Málaga. The pregnant women will be informed as follows: "If you decide to take part in the study, in addition to being given various postural recommendations, you will be included, at random, in one of the three treatment groups. In two of these, moxibustion techniques will be applied at a specific point on each foot, while in the third group the standard treatment procedures followed in the healthcare system will be applied, to see if spontaneous correction occurs. If you are assigned to one of the two groups in which moxibustion is applied, then, according to the random choice made, you may be given moxibustion at a point that has been proved to be effective, or on the contrary, at a point that has not proved to be of any value for the aims of our study". The pregnant women will also be informed of the possible risks associated with the use of moxibustion (respiratory discomfort from the smoke inhaled, the possibility of burns or of ulceration of the skin) and that they may conclude their participation in the study at any time, with no type of penalty or loss of benefits they would otherwise be entitled to.

The subjects included in the study will be pregnant women, aged at least 18 years, whose foetus is in a non cephalic position (diagnosed by physical examination and by echography), with a gestational age of 33–35 weeks (estimated by echography), normal foetal biometry, who have signed their informed consent and who have not previously received moxibustion treatment to correct the position of their unborn baby. Criteria for exclusion will include twin pregnancy, pelvic defect, previous uterine surgery, foetal malformation or chromosome disorder, uterine malformation, risk of premature birth (preterm uterine contractions and/or initial dilation or shortening of the cervix with a Bishop's score of 4), uterine fibromas > 4 cm, treatment with tocolytic drugs, heart or kidney disease affecting the mother, other pregnancy-related complications, or incapacity to complete the questionnaire or respond to the assessor's questions.

The ethical validity of this study has been analysed and approved by the Clinical Trials Ethics Committee of the Andalusian Regional Government, following approval by the corresponding Research Committee at each of the participating clinics.

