### Randomization and treatment allocation

The randomization of the three branches of the study will be carried out on a centralized basis, by a statistician who is otherwise unrelated to the study, using a 1:1:1 scheme in blocks of 12 and stratifying by clinics. There will be the same number of sets of envelopes as there are of participating midwives/clinics (some 40 midwives are expected to take part). Each set will contain 12 opaque envelopes which will be sealed after the introduction of a card with the letter corresponding to the allocation to the group as determined by the software-generated sequence: Group A (true moxibustion), Group B (sham moxibustion) and Group C (control). After the baseline assessment and the signing of informed consent, these sealed, opaque, numbered envelopes will be used in sequence to assign the study subjects to one of the three groups. The collaborating midwife will note on the card the pregnant woman number and that of the clinic. At the end of the study, the chief researcher will check each card against the original randomization list to confirm that all the subjects received the treatment that had been assigned to them. This method ensures that neither the clinics nor the healthcare professionals taking part in the study will be involved in the randomization process and thus will not be able to influence it. A patient may be withdrawn from the study at any time, at her discretion or that of the researcher. The reasons for this will be noted down on the summary page of the Data Collection Record (DCR). The midwives who participate in the study have attended a 10-hour training course on postural recommendations and moxibustion techniques, and in which criteria for data collection were standardised.

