## Discussion

As observed above, the problem identified by the analysts of the only Cochrane review available is the low methodological quality of most of the studies that have been made. In designing the present study, special care was taken regarding the characteristics conforming a quality RCT, in accordance with the recommendations made by Jadad [18]. Nevertheless, the following foreseeable limitations should be pointed out: firstly, the sample was extracted from the universe of pregnancies managed within the Andalusian Public Healthcare System (SSPA), and therefore the conclusions drawn will only be applicable to this population group. The complexity of including private clinics in the study led us to renounce this idea, especially in view of the fact that the coverage of the pregnancy control programme within the public system is almost universal; moreover, the pregnant women who make use of private systems do not stop receiving the follow-up attention scheduled under the public healthcare system. From the bibliographic review performed, neither does it seem that social class influences the incidence of breech presentation or its version during gestation. It is very likely, therefore, that the results obtained will resemble those that would be derived for the entire population of pregnant women in Andalusia. The inclusion of a routine control of the official programme (an echography performed in week 32) also avoids possible selection bias. Thus, with the involvement of the gynaecologist performing this examination, and of the midwife who participates in routine care, the uptake is ensured of 100% of the cases of NCP detected during the study period, while the rate of losses to follow up is minimised.

Secondly, there exists the possibility (which has actually occurred in other studies) of a pregnant woman refusing to take part when she discovers which branch of the research study she has been assigned to. This is applicable to the formation of the control group, as normally any intervention (whether true or sham moxibustion) will be willingly accepted by a pregnant woman in a situation of some risk. In the studies examined, this has actually occurred in only a very small percentage of cases, but note should be taken of this possible source of bias.

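### Women are told before consent that one moxibustion point is proven, against the protocol's own account of the evidence

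*Protocol article*

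**What the plan says.** The Subjects section of the protocol article prints the information that women will be given. It describes three groups. For the two moxibustion groups it says that "you may be given moxibustion at a point that has been proved to be effective" or, alternatively, "at a point that has not proved to be of any value for the aims of our study". The third group receives standard care.

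The section on randomization and treatment allocation fixes the order of events: "After the baseline assessment and the signing of informed consent, these sealed, opaque, numbered envelopes will be used in sequence".

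On the evidence, the Abstract says the technique is ancient "but as yet there is insufficient evidence of its real effectiveness". The Background reports that a Cochrane review "concluded that there is insufficient evidence from the studies included in its analysis", and that the authors' own larger review still found studies of low methodological quality. The first research question asks how effective moxibustion at BL67 is.

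On blinding, the Abstract states: "The participants in the trial will be blinded to both interventions". The Sample size section powers A or B against C, and the Statistical analysis section takes usual care as the reference level. The Discussion foresees refusal by women who learn their allocation: "This is applicable to the formation of the control group". It adds that this was rare in the studies examined.

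**The concern.** The script gives as settled fact the hypothesis that the trial exists to test. Two things are at stake.

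The first is the accuracy of the information on which women consent.

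The second is a risk to the comparisons with C. A woman in C knows that she receives neither procedure, and she has just been told that a proven one exists. That gives her a reason to withdraw or to seek moxibustion elsewhere. Outside use is plausible: the trial itself has a friend or relative give the home sessions after one training session, and the Discussion describes the procedure as simple and quickly learned. The intention-to-treat set holds only women with valid data, so controls who leave without a recorded outcome drop out of the main analysis.

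**Working it through.** **1. The texts side by side.** The script (Subjects) says one point is proven. The Abstract, the Background and the first research question treat effectiveness as unknown. These cannot all be right. The fault lies in the first half of the script's contrast: saying that the other point has not been shown to be of value is consistent with the rest of the protocol.

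**2. Timing.** Information comes first, then consent, then the envelope. Every woman in every arm hears the statement before allocation.

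**3. Who is affected.** A and B hear the same words, and the script does not say which point is which. C is the only arm whose women know what they are getting, and it is the reference arm.

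**4. The sample size is not in question.** Inputs: the 20-point difference, 90% power and 25% dropout come from the Sample size section. The rates of 70% and 50% come from the Background. A two-sided 0.05 test is assumed.

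- n per arm = [1.96·√(2·0.60·0.40) + 1.2816·√(0.70·0.30 + 0.50·0.50)]² / 0.20² = 124
- 124 / 0.75 = 165.3, so 166 per arm and 3 × 166 = 498, against 492 stated (1.2% apart)
- The unpooled variant gives 121, then 162 per arm and 486 in total.

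The stated figure is reproduced closely enough, and rewording the script would not change it.

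**5. Illustration: power lost through extra control-arm loss.** The documents give no arm-specific rate, so the loss rates are assumptions. 492 / 3 = 164 women per arm. The moxibustion arm keeps 164 × 0.75 = 123. With p̄ the pooled rate:

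z = [0.20 − 1.96·√(p̄(1−p̄)(1/n_A + 1/n_C))] / √(0.21/n_A + 0.25/n_C), and power = Φ(z).

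| Control loss | Controls analysed | Power |
|---|---|---|
| 25% | 123 | 89.8% |
| 30% | 114.8 | 88.7% |
| 35% | 106.6 | 87.5% |
| 40% | 98.4 | 86.1% |
| 50% | 82 | 82.5% |

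**6. Illustration: bias from selective loss.** Take a true control rate of 50%, a lost fraction d, and a cephalic rate p_L among lost controls (d and p_L are assumptions). The observed control rate is (0.50 − d·p_L) / (1 − d).

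| p_L | Observed rate, d = 25% | Observed rate, d = 35% | Shift at 35% |
|---|---|---|---|
| 40% | 53.3% | 55.4% | 5.4 points against moxibustion |
| 60% | 46.7% | 44.6% | 5.4 points in favour |
| 70% | 43.3% | 39.2% | 10.8 points in favour |

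Part of each shift is already there at the planned 25% loss. For p_L = 60%, going from 25% to 35% adds 5.4 − 3.3 = 2.1 points. The sign depends wholly on p_L, about which the documents say nothing.

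**The case against.** The case against reading much into this sentence is substantial.

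- **Refusals were rare.** The Discussion says so of the studies examined, and the sample size already allows 25% dropout. No passage ties refusal to this wording. This stands, although the documents do not say what women in those studies were told.
- **The outcome is objective.** Presentation at term is not a matter of opinion, so belief could act mainly through adherence, outside treatment or withdrawal. This stands.
- **The claim has some basis.** The Background estimates 70% correction against 50% in controls. But that estimate comes from studies the authors call low in quality, so it does not support calling the point proven.
- **Ethics approval was given.** That calls for caution before declaring consent invalid, but it does not reconcile the texts.

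A reader might infer more than the documents support:

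- **That the script builds expectation bias and control loss into the trial.** The documents show a possible route, not an effect.
- **That power falls sharply through contamination.** If 10% or 20% of controls obtained moxibustion with its full benefit, the contrast would be 70% against 52% or 54%, and power at 123 per arm would be 82.9% or 73.7%. The arithmetic is right, but the rates are assumed. Any open control arm that hears of moxibustion carries some of this risk under neutral wording too, and nothing in the documents gives the increment due to this sentence.
- **That the blinding check between A and B is weakened.** Both arms hear the same text, and wondering which point is real follows from disclosing a sham at all.
- **That equipoise is lost.** The Abstract and Background document the uncertainty, and a sentence to participants does not remove it. The fault is in what women are told.

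**Conclusion.** The contradiction is certain and lies in the current text: women are told before consent that one point is proven, while the protocol says that this is not established and sets out to test it. The statement should be corrected for that reason alone.

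The consequence for the results is a credible risk, confined mainly to A versus C and B versus C. It could add to control-arm refusal and to moxibustion outside the trial. Its size and direction cannot be determined from the documents. On assumed loss rates the power cost is small (about 2 points at 35% control loss, about 4 at 40%), while selective loss could shift the control rate by several points either way. A versus B is largely protected.

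**What to change.** Reword the script to say that one of the two points is traditionally used to turn the baby but that its effectiveness has not been established, and that the other is a comparison (sham) point not expected to have this effect.

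Keep the sham disclosure. The blinding question under Secondary outcomes asks women whether they think their treatment was real or sham, or whether they do not know, and this presupposes that they were told a sham exists. A text saying only that two points are used and neither is known to help would remove that.

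The cost is a short change to the information text and a minor ethics amendment. Arms, sample size and analysis stay as they are.

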### Randomization and treatment allocation

The randomization of the three branches of the study will be carried out on a centralized basis, by a statistician who is otherwise unrelated to the study, using a 1:1:1 scheme in blocks of 12 and stratifying by clinics. There will be the same number of sets of envelopes as there are of participating midwives/clinics (some 40 midwives are expected to take part). Each set will contain 12 opaque envelopes which will be sealed after the introduction of a card with the letter corresponding to the allocation to the group as determined by the software-generated sequence: Group A (true moxibustion), Group B (sham moxibustion) and Group C (control). After the baseline assessment and the signing of informed consent, these sealed, opaque, numbered envelopes will be used in sequence to assign the study subjects to one of the three groups. The collaborating midwife will note on the card the pregnant woman number and that of the clinic. At the end of the study, the chief researcher will check each card against the original randomization list to confirm that all the subjects received the treatment that had been assigned to them. This method ensures that neither the clinics nor the healthcare professionals taking part in the study will be involved in the randomization process and thus will not be able to influence it. A patient may be withdrawn from the study at any time, at her discretion or that of the researcher. The reasons for this will be noted down on the summary page of the Data Collection Record (DCR). The midwives who participate in the study have attended a 10-hour training course on postural recommendations and moxibustion techniques, and in which criteria for data collection were standardised.

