### Sample size

The sample size has been predetermined at n = 492 patients, for a significance level of 95%, a power of 90% and a difference in the success rates of either of the intervention groups (A or B) with the control group (C) of 20%, assuming a dropout rate of 25%. These values were calculated using SamplePower version 2 software.

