### Interventions

All the study subjects will be given various postural recommendations.

True moxibustion (TM): The first intervention will be made at the Healthcare Clinic. This session (overseen by the midwife responsible) will serve as a training session for the friend or relative who is to apply the remaining sessions, at home. The mother should lie down, face up, wearing comfortable clothing and with no pressure at the waist from buttons, belt, etc. and with her legs slightly bent at the knee. Heat will be applied for 20 minutes, by means of a moxa cone (herbal preparation with *Artemisia vulgaris*) at point BL67 (*Zhiyin*), close to the outer angle of the little toenail (Figure 1). The heat will be applied from a distance of 1.5–3 cm, to ensure that the subject notices a feeling of warmth in the zone, but without any pain or burning. The application site (right or left foot) will be alternated every 2 minutes or more often if any untoward sensation of heat is felt.

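### Each midwife/clinic holds one visible 12-envelope block, so the last allocations in a fully used set can be foreseen and the assurance that staff cannot influence allocation is too strong

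*Protocol article*

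**What the plan says.** All of the following is in the protocol article.

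- **Scheme** (Randomization and treatment allocation): an independent statistician prepares the list centrally, "using a 1:1:1 scheme in blocks of 12 and stratifying by clinics". There are as many envelope sets as midwives/clinics, and "some 40 midwives are expected to take part".
- **Set size** (same section): "Each set will contain 12 opaque envelopes which will be sealed after the introduction of a card with the letter corresponding to the allocation".
- **Order of use** (same section): after baseline assessment and consent, "these sealed, opaque, numbered envelopes will be used in sequence to assign the study subjects to one of the three groups".
- **Who handles the card** (same section): "The collaborating midwife will note on the card the pregnant woman number and that of the clinic".
- **Who knows the arm** (Interventions): "This session (overseen by the midwife responsible) will serve as a training session for the friend or relative". The point is BL67 for true and SP1 for sham moxibustion. The control group has standard care.
- **Who assesses** (Data collection): the midwife makes the baseline evaluation.
- **Assurance** (Randomization and treatment allocation): the method is said to ensure that clinics and professionals are not involved in randomisation and "thus will not be able to influence it".

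**The concern.** Block size and set size are both 12, so a set begins and ends with its block. Anyone who counts the envelopes knows the block size, and the three equal groups give its composition. Sealing and opacity protect the next card from being read. They do not protect it from being deduced from the cards already opened.

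The midwife's knowledge of past arms is not stated in so many words, but it follows from her tasks: she handles each card and supervises treatment at one toe point, the other, or neither. Near the end of a set she may therefore know the next arm before she assesses the next woman.

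If that knowledge affects which woman is entered, or when within the 33–35 week window, the arms can differ in prognosis from the start. The planned adjustment covers age, parity, gestational week and imbalanced baseline variables. It cannot reach selection on factors that were not recorded.

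**Working it through.** **Plan's own figure.** The section Sample size states "The sample size has been predetermined at n = 492 patients". Taking the 70% and 50% success rates in the Background as the design rates, two-sided alpha 0.05 and power 90%:

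- The pooled-variance formula gives 124 per arm; 124/0.75 = 165.3, rounded up to 166; × 3 = 498.
- The unpooled formula gives 121 per arm; 121/0.75 = 161.3, rounded up to 162; × 3 = 486.

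The stated 492 lies between these, so it reproduces. It matters here only for how far sets are used: 492/40 = 12.3 women per set, and 492/41 = 12 exactly. On average the plan expects sets to be used up or nearly so.

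**Inputs for predictability.** One block of 4 true (A), 4 sham (B) and 4 control (C) cards, opened in sequence by someone who has seen all earlier cards.

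**Exact arm.** The next arm is certain when all *r* remaining cards are the same. Before envelope 13 − *r* is opened, the probability is 3 × C(4, *r*) / C(12, *r*):

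| Envelope | Cards left | Calculation | Probability |
|---|---|---|---|
| 12 | 1 | 12/12 | 1.00 |
| 11 | 2 | 18/66 | 0.27 |
| 10 | 3 | 12/220 | 0.055 |
| 9 | 4 | 3/495 | 0.006 |

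The sum is 1.33 of 12 (11%).

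**Moxibustion (A or B) against control.** Here there are 8 cards of one kind and 4 of the other. The probability is [C(8, *r*) + C(4, *r*)] / C(12, *r*):

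| Envelope | Cards left | Calculation | Probability |
|---|---|---|---|
| 12 | 1 | 12/12 | 1.00 |
| 11 | 2 | (28 + 6)/66 | 0.52 |
| 10 | 3 | (56 + 4)/220 | 0.27 |
| 9 | 4 | (70 + 1)/495 | 0.14 |
| 8 | 5 | 56/792 | 0.07 |
| 7 | 6 | 28/924 | 0.03 |
| 6 | 7 | 8/792 | 0.01 |
| 5 | 8 | 1/495 | 0.002 |

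The sum is 2.04 of 12 (17%).

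**Weaker information.** By exact recursion over the same block, at least one arm is already ruled out for 3.47 of 12 allocations (29%). Always guessing the arm with most cards left is right for 6.14 of 12 (51%), against 33% by chance.

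**Sets that are not used up.**

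| Women entered from the set | Exact arm certain | Moxibustion vs control certain |
|---|---|---|
| 12 | 1.33 | 2.04 |
| 11 | 1.33 − 1.00 = 0.33 | 2.04 − 1.00 = 1.04 |
| 10 | 0.33 − 0.27 = 0.06 | 1.04 − 0.52 = 0.53 (before rounding) |

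Most of the certainty about the exact arm therefore comes from the 12th envelope alone.

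**The case against.** The safeguards are real: independent central generation, sealed opaque numbered envelopes, use only after consent, and a final check of each card against the list. A block of four times the number of arms is not small. The obstetrician identifies the women at the routine week-32 scan, and nothing suggests that the obstetrician sees earlier allocations. Certainty comes late in a set, and recorded baseline factors are adjusted for. All of this limits the size of the problem. It does not remove it, because none of these safeguards hides the running tally of opened cards.

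Some stronger readings are tempting but not supported:

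- *The envelopes run short.* A reader might multiply 40 by 12, get 480, and conclude that 492 cannot be reached. But the number of midwives is an approximate expectation, and 41 sets give exactly 492. Even with 480 women, 120 per arm would be evaluable instead of 123, and power would be 0.890 instead of 0.898.
- *Recruitment is capped and a fast clinic cannot offset a slow one.* The article neither describes nor excludes further envelopes. A condensed article may leave resupply to the full protocol.
- *The same midwife takes consent.* The article does not say who does.
- *A fixed number of women will have a known arm.* Multiplying 1.33 by 41 sets gives about 55 of 492, but that requires every set to be used completely.
- *The Discussion shows staff steering entry.* It describes women refusing once they know their arm, mainly in the control group. That suggests the control arm is less attractive, and no more.

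**Conclusion.** The point holds in a limited form. With one visible, complete block per set, the midwife can deduce the last allocation with certainty, the 11th about one time in four, and the split between moxibustion and control somewhat earlier. The upper figures are 1.33 of 12 for the exact arm and 2.04 of 12 for moxibustion against control.

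They rest on three assumptions: the set is fully used; one person has seen all its earlier cards, which is inferred from the midwife's tasks; and that person recognises the 4:4:4 composition.

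The assurance in the article is too strong. Staff cannot change the sequence, but they can foresee part of it before baseline assessment and entry. Nothing in the document shows that anyone would act on this, and no amount of bias can be derived from it. The finding is that the stated safeguard does not deliver what is claimed for it. It should be corrected because the remedy is cheap.

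**What to change.** - The independent statistician generates each clinic's list with randomly varying block sizes in multiples of 3, not disclosed to the sites. Blocks of 3 should be avoided: if the size is known, a third of the allocations in a block of 3 are certain beforehand, against 20% in a block of 6 and 11% in a block of 12.
- Each clinic receives more envelopes than it is expected to use, so that the end of a set does not mark the end of a block. Alternatively, each allocation is released centrally after the woman is registered.
- The assurance is reworded to say that professionals cannot alter the sequence, and to state what is done to keep the next allocation unpredictable.

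The cost is a new software-generated list and extra envelopes before recruitment, or the running of a central release. The downside is slightly looser balance between arms within a clinic.
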